## Abstract

**Background:** Imeglimin is a novel type 2 diabetes (T2D) drug that is expected to improve mitochondrial function. In its phase 3 clinical trials in Japanese patients with T2D, the hemoglobin A1c (HbA1c) decrease following imeglimin administration was slow, reaching a plateau after 20–24 weeks of treatment. In general, the erythrocyte lifespan may be a factor when HbA1c shows an abnormal value. Therefore, this study will comparatively evaluate HbA1c and other markers of glycemic control in patients with T2D after imeglimin administration and also examine the effects of imeglimin on erythrocytes.

**Methods:** This single-arm, open-label, prospective, exploratory study is designed to evaluate the divergence between HbA1c and glycoalbumin (GA) or 1,5-anhydroglucitol (1,5-AG) and the glycemic reduction rate in 30 patients with T2D with inadequate glycemic control when imeglimin 2,000 mg is administered for 6 months. In addition, we will examine the effect on erythrocytes, the presumed cause of this divergence. We will measure sustained glycemic variability using flash glucose monitoring and examine the relationship between changes in these indices and HbA1c. Moreover, because prolonged erythrocyte lifespan is a possible cause of falsely high HbA1c levels, erythrocyte lifespan, erythrocyte deformability, and hemoglobin concentration will be evaluated as effects of imeglimin on erythrocytes. Furthermore, if imeglimin has an ameliorative effect on erythrocyte deformability, it may improve peripheral arterial disease; thus, we will also evaluate the toe-brachial pressure index, a measure of this effect.

**Discussion:** In this study, if imeglimin administration results in diverging rates of hypoglycemic effect between HbA1c and GA or 1,5-AG and prolongs erythrocyte lifespan, GA and 1,5-AG, rather than HbA1c, will be considered appropriate measures of the hypoglycemic effect in the early stages of imeglimin administration. If imeglimin improves erythrocyte deformability, it may also be a new treatment strategy for peripheral arterial disease, a chronic complication of T2D.

**Ethics and dissemination:** The study protocol was scientifically and ethically reviewed and approved by the Certified Clinical Research Review Board of Toho University (approval number: THU22002). The study protocol was registered in the Japan Registry of Clinical Trials (jRCT) in December 2022 (jRCTs031220489).

## 1 Introduction

The number of patients with diabetes mellitus in Japan has increased with changes in lifestyle and the social environment. A recent survey estimated that there are 10 million people each with diabetes or prediabetes (Ministry of Health, Labour and Welfare, 2017). In addition, diabetes mellitus affects 7.6% of adults aged 20–79 years (Neville et al., 2009), and improving diabetes care is an important issue.

Imeglimin is a drug for type 2 diabetes (T2D) treatment with a novel mechanism launched in Japan in September 2021. Although it is structurally related to metformin, unlike the biguanide class of metformin, imeglimin is a new class drug of tetrahydrotriazine-containing molecules called “glimins” (Theurey et al., 2022). Imeglimin exerts its hypoglycemic effect by promoting glucose-stimulated insulin secretion and improving insulin resistance. Its mechanism of action may be mediated by an effect on the mitochondria (Hallakou-Bozec et al., 2021a), and it may improve mitochondrial function. It has also been suggested that imeglimin acts on the pancreas, skeletal muscle, and liver, three key organs involved in the pathophysiology of T2D, through targeting mitochondria and reducing oxidative stress (Hallakou-Bozec et al., 2021b).

In phase 3 clinical trials (TIMES 1–3) in Japanese patients with T2D, imeglimin, both as a single agent and in combination with other antidiabetic drugs, caused a slow decline in HbA1c that plateaued around 24 weeks after administration (Dubourg et al., 2021; Dubourg et al., 2022; Reilhac et al., 2022). In a retrospective observational study, we reported a slower decrease in HbA1c compared to glycoalbumin (GA) and a divergence in the change rate between the two when imeglimin was administered to patients with T2D (Osonoi et al., 2022a; Osonoi et al., 2022b). HbA1c levels reflect average blood glucose levels over the past 6–12 weeks, which is an indicator of long-term glycemic control, given that the erythrocyte lifespan is approximately 120 days. However, GA, a glycoprotein, is an indicator of short-term glycemic control because the half-life of albumin is shorter than that of erythrocytes at approximately 17–23 days (Takahashi et al., 2007). Therefore, GA accurately indicates changes in blood glucose levels within 2–3 weeks. However, when improvements in blood glucose levels occur in a short period of time, such as with antidiabetic drug treatment, changes in HbA1c are delayed, resulting in a transient divergence between the two. Comparing the rate of decrease from baseline in HbA1c and GA when dipeptidyl peptidase-4 (DPP-4) inhibitors are prescribed, a divergence is seen after 2 months, but thereafter, the two show almost identical trends (Shimizu et al., 2022). However, the divergence between HbA1c and GA observed with imeglimin treatment differed from the results of that report in both magnitude and duration, and short-term changes in blood glucose levels alone cannot explain this (Osonoi et al., 2022a; Osonoi et al., 2022b; Shimizu et al., 2022).

In general, factors that cause abnormal HbA1c values in the divergence between HbA1c and GA include shortening/lengthening of the erythrocyte lifespan (Panzer et al., 1982) and increased/decreased erythrocyte production (Waters et al., 1988). One of the reasons for the higher HbA1c with imeglimin treatment compared to GA may be the prolonged erythrocyte lifespan. However, erythrocyte lifespan testing is not performed in routine clinical practice.

Prolonging the erythrocyte lifespan with imeglimin administration would result in a relatively high HbA1c and a slower rate of glycemic reduction than with GA or 1,5-anhydroglucitol (1,5-AG), suggesting that evaluating the glucose-lowering effect of imeglimin using HbA1c underestimates its effectiveness. There have been no reports, other than ours, on the divergence between HbA1c and GA or 1,5-AG on the glucose-lowering effect of imeglimin in patients with T2D under clinical conditions, or on its effect on erythrocytes (Osonoi et al., 2022a; Osonoi et al., 2022b).

The purpose of the study described in this protocol is to confirm the divergence between HbA1c and the rate of glycemic reduction between GA and 1,5-AG in patients with T2D after treatment with 1,000 mg of imeglimin twice daily for 6 months. In addition, we aim to prospectively examine the effects on erythrocytes, the presumed cause of this divergence.

## 2 Methods/design

### 2.1 Design

The INFINITY study (Comparative evaluation of clinical glycemic control markers treated with ImeglimiN and its eFfect on erythrocytes IN patIents with TYpe 2 diabetes mellitus) is a single-center, single-arm, open-label, prospective study. In clinical practice, the hypoglycemic effect of imeglimin in patients with T2D may differ when measured by HbA1c and GA levels. This study will be conducted in a single-arm, exploratory study (Table 1) because the prolonging of erythrocyte lifespan is postulated as the cause of this divergence. This study will compare HbA1c with the rate of glycemic reduction over time for GA or 1.5-AG to assess whether HbA1c is an appropriate measure. Continuous blood glucose variability measured using flash glucose monitoring (FGM) will also be examined related to changes in these indices to ensure reliability. In addition, because the effect of imeglimin on erythrocyte lifespan is a possible cause of HbA1c deviation, hemoglobin concentration, erythrocyte lifespan, and erythrocyte deformability will also be examined as effects on erythrocytes. Furthermore, if imeglimin ameliorates erythrocyte deformability, it is expected to have the potential to improve peripheral arterial occlusive disease, so an index of arteriosclerosis will also be measured.

**TABLE 1 T1:** Overview of visits and tests schedule.

Item	At informed consent	Pre-observation (months)		Observation period (months)							Follow-up period (months)			At discontinuation		
		−2	−1	0	1	2	3	4	5	6	7	8	9	
Allowable ranges of visits (±weeks)		±2	±2	±2	±2	±2	±2	±2	±2	±2	±2	±2	±2			
Informed consent	X															
Demography	X															
Study drug adherence					X	X	X	X	X	X				X		
Height, body weight				X	X	X	X	X	X	X	X	X	X	X		
Blood pressure, pulse rate				X	X	X	X	X	X	X	X	X	X	X		
Blood tests		X	X	X	X	X	X	X	X	X	X	X	X	X		
Urinalysis				X	X	X	X	X	X	X	X	X	X	X		
Erythrocyte lifespan		X	X	X	X	X	X	X	X	X	X	X	X	X		
Erythrocyte deformability			X	X	X	X	X	X	X	X	X	X	X	X		
Arteriosclerosis/inflammation test				X						X			X	X		
FGM test		X	X	X	X	X	X									
Adverse events		X	X	X	X	X	X	X	X	X	X	X	X	X		

Abbreviations: FGM, flash glucose monitoring.

The observation period will be 6 months as the shortest period to confirm the divergence in the rate of glycemic reduction. The decrease in HbA1c after imeglimin administration is reportedly gradual, reaching a maximum approximately 6 months after the start of administration (Dubourg et al., 2021; Dubourg et al., 2022; Reilhac et al., 2022). In addition, a 2-month pre-treatment observation period will be set to evaluate various conditions before imeglimin administration, and a 3-month follow-up period after administration will be evaluated whether the effects of imeglimin on erythrocytes are reversible. A follow-up period of 3 months will be set to evaluate safety.

The study drug imeglimin (1,000 mg as TWYMEEG ^®^ tablets) will be administered orally twice daily, starting within 1 week after the end of the baseline examination and continuing through the observation period of 6 months. After 6 months, imeglimin will be discontinued, and the patients will be followed for 3 months. The use and dose escalation of an α-glucosidase inhibitor (α-GI) and metformin are allowed for glycemic control during the follow-up period.

The addition of all types of diabetes medications and the escalation of doses of α-GI and metformin taken during the 6-month observation period from the start of imeglimin administration (except in the case of discontinuation) are prohibited because of the possibility that these will affect the evaluation of this study. The use of antiplatelet and antithrombotic drugs is prohibited during the observation and follow-up periods.

The α-GI (excluding acarbose) and metformin used before the day of the consent will be continued in principle without dose change from the day of consent until the end of the 6-month observation period. Drugs deemed medically necessary can be added except for diabetes medications, antiplatelet agents, and antithrombotic agents.

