#### 2.3.2 Secondary outcomes

Items 1–4 below will be compared between baseline (month 0) and each time point in the pre-observation, observation, and follow-up periods, and between 6 months after imeglimin administration and each time point in the follow-up period. The change from baseline (maximum and mean values) in the pre-observation and observation periods will also be evaluated.1. Erythrocyte lifespan

Erythrocyte lifespan is calculated by measuring the carbon monoxide (CO) concentration in exhaled breath using a Carbolizer (Taiyo Co., Ltd., Osaka, Japan) and using the Strocchi et al., formula shown below (Strocchi et al., 1992):

Erythrocyte lifespan (days) = K × hemoglobin (g/mL)/endogenous CO (ppm).

K = 1380 (conversion factor).2. Erythrocyte deformability

Erythrocyte deformability is measured using a blood fluidity measuring device MC-FAN (Optima Inc., Tokyo, Japan). The microchannel array passage time of 100 μL heparinized whole blood is an index for blood fluidity.3. Red blood cell count, white blood cell count, hemoglobin concentration, and hematocrit (Ht)4. Corpuscular constant (mean corpuscular volume: MCV, mean corpuscular hemoglobin concentration: MCHC, mean corpuscular hemoglobin content: MCH)

Items 5 and 6 below will be compared between baseline and the pre-observation or observation periods.5. Measured values of HbA1c, GA, and 1,5-AG, change from baseline, and percent reduction in blood glucose with baseline as 100% (percent reduction in blood glucose will also be compared between each index at each time point)6. GA/HbA1c and 1,5-AG/HbA1c ratios

For items 7 and 8 below, data measured by the FGM system using FreeStyle Libre Pro (Abbott Diabetes Care Inc., Alameda, CA, United States of America) will be used to compare baseline with each time point during the observation period (up to 3 months after imeglimin administration). FreeStyle Libre Pro should be used following the package insert.7. Change in mean daily glucose levels and percentage decrease in blood glucose (baseline is the day before imeglimin administration)8. Mean 14-day glucose levels, estimated HbA1c levels, glucose management indicator (GMI), and respective percentage decreases in glycemia (baseline is 14 days before imeglimin administration):

Estimated HbA1c (%) = (mean glucose [mmol/L] + 2.59)/1.59.

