### 2.8 Statistical analysis

Summary statistics of the background data of the study participants will be calculated. For nominal variables, the numbers in each category and their percentages will be shown; for continuous variables, the numbers, mean, standard deviation, minimum, median, and maximum values will be calculated.

Two analysis groups will be used to assess the efficacy of this study: the full analysis set (FAS) and the per-protocol set (PPS), with FAS being the primary analysis. The FAS will be the population of eligible patients who received at least one dose of the study drug and have hemoglobin concentration measurements at baseline and at least one time point during the observation period. The PPS will be the population from the FAS, excluding those who deviated from the study protocol (e.g., use of prohibited concomitant drugs or study drug adherence of <80%). The safety analysis set (SAS) will be used to determine the safety of the study, and the SAS will be the population of patients who received at least one dose of the study drug and have data on any of the safety outcomes.

Summary statistics of hemoglobin levels before and at 6 months after imeglimin, the primary efficacy endpoint, will be calculated. A one-sample *t*-test or Wilcoxon’s signed rank test will be used to evaluate its statistical significance. For the secondary outcomes obtained from the metric data, summary statistics will be calculated for each observation point, a one-sample *t*-test or Wilcoxon’s signed rank test will be performed to evaluate statistical significance, and, if necessary, analysis of covariance, and multivariate analysis will be performed. If the data are non-normally distributed, appropriate data transformations will be applied. When statistical tests are conducted, the significance level will be set at 0.05 (two-sided), with the confidence coefficient for statistical estimation being 95% (two-sided).

In addition, the principal investigator and a biostatistician will confirm the detailed statistical analysis plan before the database is locked. All laboratory data are analyzed by an independent a biostatistician at the implemented in compliance with an outsourcing agreement.

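### A change in red-cell markers after month 6 cannot be assigned to imeglimin withdrawal alone in patients whose α-GI or metformin is started or raised in follow-up

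*Protocol article*

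**What the plan says.** Section 2.1 (Design) of the protocol article gives the post-treatment months a scientific purpose as well as a safety one: "a 3-month follow-up period after administration will be evaluated whether the effects of imeglimin on erythrocytes are reversible". Month 6 is the switch point: "After 6 months, imeglimin will be discontinued, and the patients will be followed for 3 months". For the same months the section adds: "The use and dose escalation of an α-glucosidase inhibitor (α-GI) and metformin are allowed for glycemic control during the follow-up period".

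During treatment the rule is the opposite. "The addition of all types of diabetes medications and the escalation of doses of α-GI and metformin taken during the 6-month observation period" is the subject of a ban; such changes "are prohibited because of the possibility that these will affect the evaluation of this study". α-GI and metformin already in use at consent are, in principle, kept at the same dose up to month 6. A further sentence in 2.1 lets other medically necessary drugs be added but bars diabetes drugs, and it names no period.

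Section 2.3.2 compares items 1–4 (erythrocyte lifespan, deformability, blood counts with hemoglobin, corpuscular constants) with baseline at each visit, and also "between 6 months after imeglimin administration and each time point in the follow-up period". Section 2.3.4 compares baPWV, TBI, hs-CRP and urinary 8-OHdG at baseline, month 6 and three months after withdrawal.

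Under 2.8, membership of the FAS depends on eligibility, one dose, and hemoglobin values at baseline and during treatment. The PPS is the FAS "excluding those who deviated from the study protocol (e.g., use of prohibited concomitant drugs or study drug adherence of <80" (the last figure is a percentage).

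**The concern.** A withdrawal phase asks whether a marker returns once the drug is stopped. In a single-arm trial each patient is their own control, so the contrast is clean only if nothing else relevant changes at month 6. Here the release of background therapy begins at the same moment as withdrawal. The permission is given for glycemic control, so patients whose glucose rises most off imeglimin are presumably likelier to change. That is an inference, since the article states no trigger.

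At stake is the reading of the contrasts from month 6 to months 7, 8 and 9. In patients who change therapy, an added or raised drug, or its glycemic effect, could mask a true reversal or produce an apparent one. The comparison as written cannot tell these apart.

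**Working it through.** **1. What changes when (sections 2.1, 2.3.2, 2.3.4)**

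| Period | Imeglimin | α-GI and metformin | Outcomes compared |
|---|---|---|---|
| Months −2 to 0 | none | held | items 1–4 |
| Months 0 to 6 | given | held | items 1–4; exploratory markers at 0 and 6 |
| Months 6 to 9 | stopped | may be used and raised | items 1–4 at 7, 8, 9; exploratory markers at 9 |

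Only one treatment factor changes at month 0. Two may change at month 6.

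**2. Analysis sets.** FAS membership is settled by month 6. The PPS removes protocol deviations, and a permitted change is not a deviation. Follow-up changes in α-GI or metformin therefore remain in both sets.

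**3. Other analyses.** Section 2.8 allows analysis of covariance and multivariate analysis if necessary. Section 2.3.4 lists an exploratory stratified analysis by antidiabetic drug. Neither is tied to drug changes made in follow-up.

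**4. The plan's own figure.** Section 2.6 uses a hemoglobin change of 0.7 g/dL, SD 1.0 g/dL, two-sided α 0.05 and 90% power. For a one-sample t-test, power comes from the noncentral t with n − 1 degrees of freedom and noncentrality (0.7/1.0)·√n. This gives 89.4% at n = 23 and 90.7% at n = 24, so the stated 24 is reproduced. 24/(1 − 0.20) = 30 matches the target, with an implied dropout of 20% that the article does not state. This calculation concerns month 0 to 6 and is not in question.

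**5. Illustration for month 6 to 9.** The bias cannot be computed from the document. Assume that a share q of patients changes therapy, that the change shifts hemoglobin by b g/dL, and that n = 24 and SD 1.0 carry over. Then bias = q × b; for example 0.50 × 0.5 = 0.25 g/dL.

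| q | b (g/dL) | Bias (g/dL) | Chance of a significant change when true reversal is 0 | Power for a true 0.7 reversal if the shift opposes it |
|---|---|---|---|---|
| any | 0 | 0 | 5.0% | 90.7% |
| 25% | 0.1 | 0.025 | 5.2% | 88.6% |
| 25% | 0.5 | 0.125 | 9.0% | 77.0% |
| 50% | 0.5 | 0.25 | 21.7% | 56.0% |
| 75% | 0.5 | 0.375 | 42.1% | 33.2% |
| 75% | 0.7 | 0.525 | 69.3% | 13.0% |

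q and b are assumptions. The table ignores the small extra variance q(1 − q)b²; at q = 50%, b = 0.7 this is 0.25 × 0.49 = 0.1225, which raises the SD from 1.00 to √1.1225 = 1.06.

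**6. What an analysis restricted to unchanged patients can show.** With n = 24(1 − q), the 95% half-width is t(0.975, n − 1) × 1.0/√n.

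| q | n | Half-width (g/dL) | Power for 0.7 g/dL |
|---|---|---|---|
| 0 | 24 | 2.069/4.899 = 0.42 | 90.7% |
| 25% | 18 | 2.110/4.243 = 0.50 | 79.9% |
| 50% | 12 | 2.201/3.464 = 0.64 | 59.9% |
| 75% | 6 | 2.571/2.449 = 1.05 | 28.7% |

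**The case against.** The strongest reply is that the ban and the permission need not conflict. Section 2.1 ties the six-month period to divergence in glycemic reduction. HbA1c, GA, 1,5-AG and their ratios (items 5–6) are compared only up to month 6, and the glucose-monitor items 7–8 only to month 3. The stated reason for the ban may therefore mainly protect glycemic markers. A reader might infer that the plan concedes an effect of α-GI or metformin on red-cell outcomes; it does not say so, and nothing in the article shows such an effect. The remark on imeglimin, "Although it is structurally related to metformin", is no evidence either, because the same sentence goes on to set imeglimin apart from the biguanides. This part of the reply stands, and it is why zero bias must be kept as a possibility.

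A reader might also infer that the off-drug phase is the trial's only evidence linking a red-cell change to imeglimin. It is not: Table 1 provides run-in visits (lifespan and blood tests at months −2, −1 and 0, deformability at −1 and 0) and monthly visits on treatment. The off-drug phase is, however, the only test of reversal.

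A third tempting step is to make visits before any drug change the main analysis. That would select on events after withdrawal that probably track glucose. It would also drop late visits, where reversal should be clearest if erythrocytes live about 120 days (Introduction). The all-visits comparison is the better main analysis.

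Finally, handling of permitted drugs is often left to the SAP, and the study is declared exploratory. The point here is narrower: the article itself fixes both the comparison and the permission that blurs it.

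**Conclusion.** The point holds as an attribution problem in secondary and exploratory comparisons. In patients whose α-GI or metformin is started or raised after month 6, the follow-up contrasts estimate the joint effect of stopping imeglimin and changing other therapy. No stated analysis separates the two.

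Its size is not known. In the illustration it runs from nothing (b = 0) to a bias of 0.525 g/dL in hemoglobin, in either direction, on assumed values of q and b. The changes are allowed, not required, so the problem arises only in patients who make them. The word for use of these drugs could cover continuation as well as starting, but dose escalation is explicit. The primary outcome and the sample size of 24 (target 30) are unaffected.

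**What to change.** Leave the treatment rule as it is and keep the all-visits comparison as the main analysis. Before database lock:

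- Record the date of every start or dose increase of α-GI or metformin through month 9, and report how many patients changed and at which visit. The PPS rule already needs concomitant-drug data; confirm that collection extends through follow-up.
- Pre-specify a sensitivity analysis of all follow-up contrasts (items 1–4 and the month-9 exploratory markers) that uses, for each patient, only visits before any such change.
- Attribute reversal, or its absence, to imeglimin withdrawal only if the estimates and confidence intervals of the two analyses are consistent. An interval too wide to exclude either no reversal or full reversal should be called uninformative, not agreement.
- Otherwise describe the result as the effect of stopping imeglimin with background therapy adjusted as needed.
- Reconcile the sentence in 2.1 that bars added diabetes drugs without naming a period with the follow-up permission.

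The cost is analysis wording and dated drug records. The downside is that the sensitivity analysis has fewer patients and is itself selective, so it can qualify the main result but not replace it.
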